## Abstract

**Background:**

The use of naloxone, an opioid antagonist, is a critical component of the US response to fatal opioid-involved overdoses. The importance and utility of naloxone in preventing fatal overdoses have been widely declaimed by medical associations and government officials and are supported by strong research evidence. Still, there are gaps in the current US national strategy because many opioid-involved overdose fatalities have no evidence of naloxone administration. Improving the likelihood that naloxone will be used to prevent fatal overdoses is predicated on facilitating an environment wherein naloxone is available near each overdose and can be accessed by someone who is willing and able to use it. How to accomplish this on a national scale has been unclear. However, there exists a national network of >1 million cardiopulmonary resuscitation (CPR) layperson responders and 4800 emergency responder agencies linked through a mobile phone app called *PulsePoint Respond*. *PulsePoint* responders certify that they are trained to administer CPR and are willing to respond to possible cardiac events in public. When such an event occurs near their mobile phone’s location, they receive an alert to respond. These motivated citizens are ideally positioned to carry naloxone and reverse overdoses that occur in public.

**Objective:**

This randomized controlled trial will examine the feasibility of recruiting first responder agencies and layperson CPR responders who already use *PulsePoint* to obtain overdose education and carry naloxone.

**Methods:**

This will be a 3-arm parallel-group randomized controlled trial. We will randomly select 180 first responder agencies from the population of agencies contracting with the PulsePoint Foundation. The 3 study arms will include a standard recruitment arm, a misperception-correction recruitment arm, and a control arm (1:1:1 allocation, with random allocation stratified by zip code designation [rural or nonrural]). We will study agency recruitment and, among the agencies we successfully recruit, responder certification of receiving overdose and naloxone education, carrying naloxone, or both. Hypothesis 1 contrasts agency recruitment success between arms 1 and 2, and hypothesis 2 contrasts the ratios of layperson certification across all 3 arms. The primary analyses will be a logistic regression comparing the recruitment rates among the arms, adjusting for rural or nonrural zip code designation.

**Results:**

This study was reviewed by the Indiana University Institutional Review Board (20218 and 20219). This project was funded beginning September 14, 2023, by the National Institute on Drug Abuse.

**Conclusions:**

The hypotheses in this study will test whether a specific type of messaging is particularly effective in recruiting agencies and layperson responders. Although we hypothesize that arm 2 will outperform the other arms, our intention is to use the best-performing approach in the next phase of this study if any of our approaches demonstrates feasibility.

**Trial Registration:**

OSF Registries osf.io/egn3z; https://osf.io/egn3z

**International Registered Report Identifier (IRRID):**

PRR1-10.2196/57280

## Introduction

### Background

In 2017, the US Acting Secretary of Health and Human Services formally declared that the opioid overdose crisis in the United States is a public health emergency [1]. Since that time, the prevalence of morbidity and mortality related to opioid overdoses has gotten substantively worse [2]. Beyond the prima facie impact of tens of thousands of overdose-involved deaths annually, the secondary impacts of the crisis strain the health care system across numerous axes; for example, even in 2013, when annual fatal prescription overdose incidence was “only” 16,235 persons, scientists at the Centers for Disease Control and Prevention found that these fatal cases accrued US $21.5 billion in costs [3]. The magnitude of the emergency is such that even in the midst of major global news on multiple fronts, news stories about fatal opioid overdoses are ubiquitous, often with calls from family members to build awareness and seek solutions [4]. Overdose and harm reduction strategies (including naloxone administration) have also received direct attention from the federal government, including as part of the 2023 State of the Union address [5].

### Naloxone Is a Critical Part of the US Overdose Emergency Response

Naloxone (including Narcan, Kloxxado, Evzio, Zimhi, and other formulations) is an opioid antagonist that can be used to reverse an opioid overdose and restore breathing, converting a potentially fatal overdose into a nonfatal overdose [6,7]. Even before the formal declaration of a public health emergency around opioids, the Department of Health and Human Services included expanded use and distribution of naloxone in its 3 priority areas to address the overdose epidemic [8]. The importance and utility of naloxone have been widely declaimed, including by the American Medical Association (“should be available almost everywhere”) [9], the American Society of Addiction Medicine (“remarkably effective, inexpensive and safe”) [10], and the US Surgeon General (“Be Prepared. Get Naloxone. Save a Life.”) [11]. Such statements are predicated on strong evidence of, and arguments for, naloxone’s effectiveness and utility in reducing fatal opioid-involved overdoses [12-16].

### Barriers Exist That Inhibit Proliferation of Expedient and Effective Overdose Responses

Data from 2019 indicate that in the majority of fatal opioid-involved overdoses, there is no evidence of naloxone administration [17]. Given the current evidence for the effectiveness of overdose education and naloxone distribution (OEND) programs [12-16], the national expansion of such programs [18,19], and simultaneous high rates of fatal opioid-involved overdoses without naloxone administration [17], we might reasonably conclude that there are one or more gaps in the current US national approach to opioid-involved overdose reversal.

For many years, the lack of availability of naloxone has been seen as a primary barrier. Most states have passed legislation intended to increase layperson access to naloxone and provide limited legal immunity to those who administer naloxone to persons experiencing an opioid-related overdose [10]. By 2021, a total of 47 states and Washington, District of Columbia, had enacted both Good Samaritan and naloxone access laws [20], and programs to facilitate distribution of naloxone to laypersons have steadily become more common [18], especially since 2010 [19]. Unfortunately, a 2018 study in Indiana and Arizona found that such policies did not always sufficiently facilitate layperson access [21]. The availability of naloxone *at cost* will likely increase in the United States in the next several years given a recent 19-0 US Food and Drug Administration advisory committee vote in favor of granting some naloxone products over-the-counter (OTC) status [22]. However, national data from a similar OTC change in Australia suggest that people may not automatically begin purchasing naloxone in response [23] (eg, other factors such as willingness may be salient).

More ubiquity in carrying and being willing to use naloxone is critical because, as described by Kim et al [24], the efficacy of naloxone is fundamentally time dependent. Brain injury from hypoxia is more likely the longer oxygen deprivation occurs [25]. In some cases, overdose death from heroin can be extremely rapid [26], and death typically occurs within 1 to 3 hours [27]. Overdoses from fentanyl and fentanyl analogs often present differently than other opioid overdoses and may be even more likely to rapidly result in fatality [28]. Thus, it is important that naloxone is *present at or near the scene* and *used as quickly as possible.* Unfortunately, despite a surge in OEND programs in the United States, relatively few people carry and are willing to use naloxone [29].

### Misperceptions About Naloxone and Overdose May Inhibit OEND Programs

Evidence suggests that misperceptions about overdose and naloxone, as well as stigmatizing beliefs about people who use drugs, may affect both layperson and first responder willingness and interest in carrying and using naloxone [29-33]; for example, first responders may be ambivalent about “providing naloxone to those they deem undeserving” [34], and a review found that stigmatizing attitudes among first responders may reduce the likelihood of bystander response [35]. Some first responders have noted that laypersons in their communities may fear “real and perceived cultural opposition” to harm reduction strategies [36]. Such reticence and stigma may even persist after OEND training [29,37] and have been described as fundamentally hindering the US response to the opioid overdose crisis [38].

To the best of our knowledge, the prevalence of specific belief statements about naloxone and overdose that do not align with current scientific evidence had not been explored in depth until 2022 [39]. We conducted a study (using the Prolific platform) consisting of 702 respondents who were representative of the US adult population across race, ethnicity, gender, and age. Several misperceptions around naloxone and overdose were fairly common in our sample, and there was a surprisingly large minority of participants (approximately one-seventh of the sample) who believed that users could “get high on naloxone” [39]. We also observed potential evidence of cognitive dissonance about OEND; specifically, large latent profiles simultaneously believed, in the framed context of naloxone reversing an opioid overdose, that “if trained and provided with naloxone, bystanders can effectively prevent overdoses in the community” and “opioid users will use more opioids if they know they have access to naloxone” [39].

### Our Proposed Study to Mitigate Barriers to Effective Overdose Response

Improving the likelihood that naloxone will be used to prevent fatal overdose is logically predicated on facilitating an environment wherein naloxone is available near each overdose and can be accessed by someone who is willing and able to use it. Conceptually, in a given community, the likelihood of an opioid overdose in the given community being reversed with naloxone is proportional to the likelihood that a trained person with access to naloxone is nearby, willing to administer it, and aware of the need. As noted, current approaches to OEND have not succeeded in reaching the threshold of sufficient coverage. With too few trained persons and sparse coverage, overdose survivability can be subject to the whims of chance, something implicitly recognized even in how lay news sometimes covers overdose reversals (“finds herself in the right place at the right time” [40]).

Recent, innovative pilot work demonstrated that a smartphone app (*UnityPhilly*) could support overdose reversal in a small group of volunteers [41]. Other innovative projects include multifaceted technology-based efforts by Brave Technology Co-Op [42]. In these cases, building to scale will take substantial time and investment. However, it may also be possible to integrate OEND within widespread but existing systems that perform other but similar services. Our particular interest is in a large, highly engaged system for cardiopulmonary resuscitation (CPR) that already exists nationally (*PulsePoint*), with >1,085,000 active monthly layperson users across approximately 4800 communities overseen by >755 agencies [43]. These individuals respond to unconscious and unresponsive persons within a prespecified radius of their smartphone based on alerts generated by local first responder agencies. While *PulsePoint* does not specifically generate alerts for an opioid overdose, the designation *unconscious and unresponsive* can refer to individuals possibly in need of CPR or those who may need overdose reversal; therefore, these laypersons are likely already responding to possible overdoses. However, they are neither systematically being encouraged to receive training around overdose and naloxone nor being reminded to carry naloxone.

We believe that the *PulsePoint* network may be an effective means of achieving widespread OEND coverage in the United States. With this preliminary study, our goal is to better understand whether and how it is feasible to recruit first responder organizations and *PulsePoint*-connected laypersons to broaden the scope of their voluntary service to include opioid overdose reversal.

### Objectives

#### Overview

We will conduct a feasibility trial to assess whether, in a random sample of 180 agencies where *PulsePoint* is already active, revised procedures (hereinafter *PulsePoint-OD*) to facilitate OEND can successfully recruit first responder agencies and layperson responders. For this study, *agency* refers to a single implementation site where *PulsePoint* is active and that is bound by the service area or jurisdiction of the first responder agency collaborating with *PulsePoint* (we provide more detailed information about agencies in the *Methods* section).

Using a parallel-group randomized controlled trial design, we will randomize 180 agencies using a 1:1:1 allocation ratio within strata to 1 of 3 arms: arm 1 (*PulsePoint-OD*, which will include the recruitment of coordinating community first responder agencies; targeted recruitment, eg, push messages, aimed toward 100% of the active *PulsePoint* users in these communities; ongoing solicitation for training of these users; and naloxone facilitation), arm 2 (same as arm 1 but with stigma-focused misinformation-debunking messages embedded), or arm 3 (a control condition).

#### Hypotheses

We will test the following hypotheses:

H1: more first responder agencies will be successfully recruited by arm 2 than by arm 1.H2: more layperson responders will report engaging with OEND programming in arm 2 than in arms 1 or 3 and in arm 1 than in arm 3.

As an exploratory follow-up, we will conduct incentivized qualitative follow-up interviews with agencies to better understand barriers to participation and how to improve uptake feasibility.

## Methods

As the participant types for H1 and H2 are different, we provide separate methodologies for each hypothesis. A conceptual diagram of the study and hypotheses is provided in Figure 1.

**Figure 1 figure1:**
[figure not shown]
Conceptual diagram of the study and hypotheses. OEND: overdose education and naloxone distribution.

### H1: First Responder Agencies

#### Parameters

The following parameters describe the interrelationships between communities and agencies for this study:

The PulsePoint Foundation reports that approximately 4800 communities currently use the *PulsePoint* app.Community participation and the use of the *PulsePoint* app are supported by agency contract holders; there are >755 such contracts in place.A contract-holding agency can serve multiple communities (eg, a county 911 office can offer *PulsePoint* to 9 different communities in the county, such as townships). An agency can also serve a single community (eg, a city fire department can offer *PulsePoint* to that city only).Any number of *additional* first responder agencies (eg, fire or police departments, emergency medical services, 911 call centers, or related entities) can contribute to a community or cluster of communities covered by a single *PulsePoint* contract, but these agencies are not contract holders.

When *PulsePoint* is introduced to a community for layperson use, the PulsePoint Foundation neither directly recruits nor interfaces with individual lay responders. Instead, the contracted first responder agencies conduct local recruitment and have the ability to send *push messages* (app-driven notices and messages) to users. Therefore, to integrate OEND into the *PulsePoint* network (eg, *PulsePoint-OD*) and for our study team to directly contact the subset of active users within each study community, it is necessary that the contract-holding first responder agencies in each community agree to participate. This first phase of the overall study (and the first hypothesis) pertains to agency-level recruitment.

#### Participants, Eligibility, and Assignment

We will use the complete list of *PulsePoint* contracting agencies as constituted approximately 3 months before the study start date (to ensure sufficient experience with the *PulsePoint* program) as the population from which to draw a random sample. At present, this list includes >755 agencies, but the actual number will vary depending on the final start date and changes in *PulsePoint* membership.

All active agencies on the final list will be eligible for sampling and randomization, with 2 exceptions. First, an agency will be excluded (and a replacement resampled and assigned to the same study arm) if further communication identifies that it is not actually a *PulsePoint* subscriber. Second, we will exclude agencies a priori or a posteriori if we learn of a similar project being conducted, or having been conducted, with *PulsePoint* with the agency. Random sampling of communities will be accomplished by having a study statistician generate a random sequence of numbers, including all values between *1* and *X*, where *X* is the total number of eligible agencies. These numbers will be directly overlaid on the list of agencies, and agencies with the lowest 180 numbers will be selected. These numbers will also be carried forward to indicate the random arm assignment.

Agencies will be randomly assigned to a study arm using stratified allocation, with a 1:1:1 allocation ratio. Specifically, one-third of the rural agencies will be randomly assigned to each study arm, and separately, one-third of the nonrural agencies will be randomly assigned to each study arm. We will determine rural status using the definition from the US Office of Management and Budget (zip codes within metropolitan areas with an urban core of ≥50,000 people are not rural, and all other areas are rural [44]). In cases where agencies hold *PulsePoint* contracts that cover both rural and nonrural areas, we will assign a status based on the location of the numeric majority of the population in the area. Arm assignment will be according to sequential numbers (from the simple random sample; therefore, this allocation approach is also by definition random) within each stratum (eg, if there are 60 rural agencies, the 20 rural agencies with the lowest random numbers will be assigned to arm 1). This procedure will ensure allocation concealment from the rest of the investigative team until the moment of assignment. Agencies will not be informed that they have been assigned to a specific trial arm; they will simply be contacted using the procedures developed for that arm. Thus, this can be considered a blinded trial.

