##### Materials

Members of our project staff will develop a short visual presentation to be used as a guideline for videoconference recruitment, along with a parallel set of core written or verbal statements reflecting the content of the presentation in cases where only telephone calls are possible. Drawing lessons from our previous successful agency and organization recruitment experiences [46-49], both the presentation and written statements will cover a limited list of important concepts that need to be imparted (eg, “Participating in this project will require very little time from your agency – we are only asking you to send out one push message each month.”). While moving through these concepts, we will allow conversation to flow freely (eg, semistructured messaging) and also use live documentation of key concepts to ensure message fidelity.

The tangible documentation will consist of digital flyers based on the open-source marketing tools developed by the PulsePoint Foundation for general community agency recruitment, including the use of similar graphical assets and fonts. However, flyers will be differentiated sufficiently from the default *PulsePoint* flyers to make it clear that the organization itself is not conducting this project (eg, we will not use the *PulsePoint* logo). For reference, *PulsePoint*-branded recruitment flyers can be viewed by clicking on the hyperlink provided in the associated reference [50]. As community agencies have already committed to offering standard *PulsePoint* services, we expect that distributing these modified documents to agencies will be a high-leverage recruitment approach. Key messaging will be drawn from local demonstration projects by the study team (eg, “Be a Lifesaver” and “Citizen Opioid Responders”) [51] as well as general marketing and recruitment principles.

As supplemental recruitment content, exemplar videos will be drawn from work produced by the Dearborn County Health Department in Lawrenceburg, Indiana, in collaboration with the study authors to create awareness of this type of initiative and will be included as web links to YouTube versions of the videos [51].

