##### After Recruitment

When communities agree to participate, they will be asked to sign an MOU regarding their participation and to respond to a small set of readiness and implementation items, such as whether the organization is already involved in naloxone distribution and whether there are local laws pertaining to opioid overdose reversal. This information will be used to locally tailor piped text into messages used for H2 (layperson recruitment).

#### Intervention (Recruitment) Arm 2

The recruitment procedures for arm 2 will be similar to those outlined for arm 1. The primary difference will be that the messaging in arm 2 will proactively address several misperceptions or stigmatizing ideas about overdose and naloxone that our recent research has suggested may be prevalent [39]. In particular, content in the fact sheets and scripts for recruitment used in arm 2 will address and preempt the following scientifically unsupported ideas (potentially among others):

“Naloxone causes risk compensation or presents a moral hazard”: it is fairly well established that OEND is not associated with increased opioid use [52-55], nor is it associated with reduced risk perceptions for heroin use [56].“Repeated overdoses are inevitable and people who experience nonfatal overdoses will die of an overdose in the near future”: while individuals who nonfatally overdose are at meaningfully increased risk, especially if they do not matriculate into a cascade of care, the substantive majority will not overdose again in the near future, and even fewer will die of a fatal overdose in the near future [57-60].“Individuals can get high from naloxone”: while this is not possible [6], our study found that 14.2% of our nationally-representative sample still believed this claim [39] to some extent.

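### Agencies can be excluded after randomisation if a similar PulsePoint project comes to light, and nothing stops that discovery, and so removal from the H1 metric M, from depending on arm or outcome

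*Protocol article*

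**What the plan says.** Two exclusions are listed under Participants, Eligibility, and Assignment in the protocol article.

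- Non-subscribers: "an agency will be excluded (and a replacement resampled and assigned to the same study arm) if further communication identifies" that the agency does not subscribe to PulsePoint. The replacement is tied to the arm. Its rurality stratum is not mentioned.
- Similar projects: "we will exclude agencies a priori or a posteriori if we learn of a similar project being conducted", or having been conducted, with PulsePoint at that agency. Nothing is said about replacement, about a date limit, about who decides, or about whether a removed agency stays in the H1 analysis.

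The random numbers used for sampling also fix the arm: "These numbers will also be carried forward to indicate the random arm assignment". Concealment is time-limited: "This procedure will ensure allocation concealment from the rest of the investigative team until the moment of assignment". Agencies are not told their arm, but "they will simply be contacted using the procedures developed for that arm". The Materials section makes the recruitment conversation semistructured. After Recruitment says that agencies that agree are asked readiness items, "such as whether the organization is already involved in naloxone distribution".

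The H1 outcome M is the number of agencies agreeing (R>0) divided by the number with which contact has been established (A>0). The H1 power statement rests on 60 agencies in each of arms 1 and 2.

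**The concern.** A project completed before assignment is a baseline fact. Excluding on it would be harmless if it were looked for in the same way in every agency and judged without knowledge of arm or result. The protocol secures neither condition: the trigger is whatever the team happens to learn.

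Discovery can follow the arm, because arms 1 and 2 hold different conversations by design. It can follow the outcome, because an agency that engages has more occasion to mention other work, and one that agrees is asked about existing naloxone activity while one that declines is not. Agreement is the numerator of M. Removing an agreeing agency lowers M and removing a declining one raises it. The wording also covers ongoing projects without a date, so one that starts after assignment could count.

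What is at stake is the comparability that randomisation gives to H1, and the recruitment rate itself, which is the main feasibility result of the study. If removed agencies are not replaced, the arms also fall below the 60 assumed for power.

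**Working it through.** **Step 1: the stated power.** Inputs from H1: Sample Size, Power, and Analysis: n = 60 per arm, 30% vs 55%, two-sided alpha 0.05.

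With pooled variance, z = [0.25·√n − 1.96·√(2·0.425·0.575)] / √(0.30·0.70 + 0.55·0.45).

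- n = 60: (1.936 − 1.370)/0.676 = 0.837, power 79.9%. Exact enumeration of the chi-square test gives 80.6%. The stated 80% reproduces.
- n = 54 (six unreplaced exclusions per arm, assumed): (1.837 − 1.370)/0.676 = 0.690, power 75.5%. Exact: 74.7%.
- Other sizes, pooled formula: 77.8% at 57 per arm and 70.4% at 48.

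**Step 2: effect of selective discovery.** The protocol gives no prevalence, so everything below is assumed: prevalence q of a similar project of 5%, 10% or 20%, unrelated to willingness to join; all 60 agencies per arm contacted; discovery probability s_a among agreeing and s_n among declining agencies. The observed rate is

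r = p(1 − q·s_a) / [p(1 − q·s_a) + (1 − p)(1 − q·s_n)].

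Example with p = 0.30, q = 0.10, s_a = 1, s_n = 0: 0.27/(0.27 + 0.70) = 27.8%.

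With no true difference (30% in both arms), observed arm 1 vs arm 2 and exact type I error at the retained numbers are:

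| Discovery pattern | q = 5% | q = 10% | q = 20% |
|---|---|---|---|
| Agreeing agencies only, both arms | 28.9% vs 28.9%; 5.2% | 27.8% vs 27.8%; 5.1% | 25.5% vs 25.5%; 5.0% |
| Agreeing only in arm 1, all agencies in arm 2 | 28.9% vs 30%; 5.3% | 27.8% vs 30%; 5.7% | 25.5% vs 30%; 8.6% |
| Extreme: agreeing only in arm 1, declining only in arm 2 | 28.9% vs 31.1%; 5.8% | 27.8% vs 32.3%; 8.0% | 25.5% vs 34.9%; 17.7% |

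For reference, the same test with no exclusions (60 vs 60) has an exact type I error of 5.2%.

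With true rates of 30% vs 55% and the first pattern, the observed contrast is 28.9% vs 53.7%, 27.8% vs 52.4% and 25.5% vs 49.4%. The difference shrinks only from 25 to 24.8, 24.6 and 23.9 points.

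**Step 3: the direction is not fixed.** Starting from 18/60 = 30%, removing five declining agencies gives 18/55 = 32.7%, and removing five agreeing ones gives 13/55 = 23.6%. These counts are illustrative and have no source in the protocol.

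**The case against.** The strongest reply is that the routes of discovery are inferred. The rule speaks only of learning of a project and names no channel. The section on establishing correspondence with local decision makers describes finding and verifying the contact person before recruitment begins, so a similar project could surface there, before any arm-specific message. The readiness item asks about naloxone distribution, which is much broader than a similar project with PulsePoint. Its stated use is to tailor messages for H2, and nothing makes it an eligibility screen. No section says who decides exclusions. All of this stands, and it is why the point is that removal can depend on arm and outcome. A reader might infer that it does; the documents do not show that.

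It is also fair that the size is speculative. For a rule confined to PulsePoint projects, a prevalence of 20% has no support in the text, and the large type I error needs opposite discovery patterns in the two arms. Silence on replacement does not mean there will be none. Excluding previously exposed agencies is a defensible eligibility choice, and the authors commit to cautious interpretation of a feasibility trial.

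What the reply does not meet is that the rule, followed as written, permits removal after assignment with no time limit, no uniform ascertainment and no blind decision. An earlier contact stage at which a project might surface does not confine exclusions to that stage.

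The wording "a replacement resampled and assigned to the same study arm" for non-subscribers is a smaller, separate matter. It could disturb the balance within rurality strata, but rurality is already a planned covariate.

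**Conclusion.** The point holds as a weakness in the exclusion rule, and the rule should be changed. The protocol allows post-randomisation removal from M on information whose discovery can differ by arm and by outcome.

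The likely effect is small if similar projects are rare. The documents give no prevalence, so the size cannot be settled. Under the assumed 5% to 20%, equal discovery confined to agreeing agencies leaves the H1 test valid but understates the recruitment rate by about 1 to 4.5 points (30% becomes 28.9% to 25.5%). Discovery that differs by arm gives a type I error of about 5% to 9%. Values up to 17.7% arise only in the extreme pattern.

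The loss of power to about 75% applies only if six agencies per arm are excluded and not replaced. A reader might conclude that the stated sample size or power is wrong. It is not: 80% at 60 per arm reproduces.

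**What to change.** 1. Apply the similar-project exclusion only on information obtained before arms are released, using whatever sources are available for all sampled agencies alike. The protocol does not show that the PulsePoint Foundation records such projects, so the source should be named and not presumed.
2. After release, keep every true subscriber in the H1 analysis as randomised. Flag similar projects found later, with the flag decided blind to arm and outcome, and report a sensitivity analysis without the flagged agencies.
3. Draw any replacement for a non-subscriber from the same rurality stratum, using the next unused random number.

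Keeping subscribers as randomised preserves 60 per arm and the stated power. The cost is a few sentences of protocol wording and one uniform check before arm release; no data had been collected at submission. The downside is that a few previously exposed agencies stay in the primary analysis, which the sensitivity analysis makes visible.
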